### Outcome measures

The primary outcome measure will be participants’ reported level of burnout assessed by the MBI-GS [4]. The MBI-GS comprises 16 items clustered in three subscales: (a) emotional exhaustion, which describes feelings of being physically and emotionally depleted; (b) cynicism, which describes an indifferent attitude and feelings of skepticism toward the nature and significance of one’s work; and (c) professional efficacy, which describes feelings of achievement and confidence in one’s work. The MBI-GS has been shown to have strong validity and reliability [33]. Secondary outcomes will be assessed by using the Death Attitude Profile-Revised [34] (death attitude), the Five Facet Mindfulness Questionnaire [35] (emotional regulation), the Ego-Resilience Scale [36] (resilience), the Self-Compassion Scale Short-Form [37] (compassion), and the World Health Organization Quality of Life Scale-8 [38] (quality of life). See Fig. 2 for schedule of enrollment, intervention, and assessment.

**Fig. 2 Fig2:**
[figure not shown]
Schedule of enrollment, intervention, and assessment

### Demographic measures

To determine whether demographic variables are potential confounding factors that affect primary and secondary outcome variables, basic demographic data (i.e., age, gender, ethnicity, marital status, education, and religion) will be collected from participants during baseline assessment. Information regarding nature of employment (i.e., full-time and part-time), professional roles (i.e., physician, nurse, social worker, personal care worker, psychological staff, and program staff), and years of professional experience in EoL care will also be collected at baseline.

### Qualitative outcome evaluation

Together with the quantitative assessment, a series of simple open-ended evaluative questions will be used to seek participants’ insights into their experience with the MCAT intervention, the impact of MCAT on their professional and personal lives, and their views on taking part in this study. Participants will be asked to provide written responses to these questions during the immediate post-intervention assessment. Also, large group sharing from each MCAT intervention session and all reflective writings produced during the intervention will be recorded, documented, and transcribed for analysis to identify insights into concerns which might impact intervention effectiveness. One in two group sharing transcripts will be randomly selected for review by the principal investigator and one co-investigator for data monitoring and quality and safety assurance.

### Acceptability and feasibility assessment

To assess feasibility in implementation and delivery of MCAT in community settings, the following will be recorded: (a) time needed to organize and conduct the intervention sessions and transcribe group sharing, (b) deviations from the intervention protocol, (c) uncompleted interventions and their reasons, and (d) MCAT interventionists’ perceptions of competence. MCAT interventionists will also record the fidelity of the intervention, experiences of intervention delivery, observations of participants’ experiences and responses during and after intervention, and any difficult or deviant cases. To assess acceptability, two acceptability focus groups comprising six to eight randomly selected MCAT participants will be conducted after completion of all interventions to elicit (1) experiences of intervention, (2) insights into which intervention components work best for them and under what circumstances, (3) insights into concerns which might impact intervention effectiveness, (4) factors that draw their participation and sustained engagement, (5) factors that deter them from sustainable practice, (6) factors that may lead other EoL care professionals to be more inclined to partake in such a program, and (7) ideas and suggestions to make the program more appealing to different types of care workers. All focus groups will be recorded and transcribed verbatim for analyses. Finally, data generated from the qualitative evaluation will serve to inform the acceptability and feasibility study.

### Data analysis

#### Quantitative data

All quantitative data will be entered, stored, and analyzed by using SPSS statistical analysis software. Between- and within-subject comparisons of outcomes will be conducted by using repeated-measures analysis of variance (ANOVA) with the appropriate confidence interval and effect size estimates reported. Intervention and waitlist-control groups will be compared to assess intervention effectiveness on the primary outcome of burnout (continuous variable); secondary outcomes, including death attitude, emotional regulation, resilience, compassion, and quality of life (continuous variables), will also be compared to examine the potential effects of MCAT on other domains of psycho-socio-spiritual well-being. Between-subject comparisons will be conducted at T2 with baseline assessment. To explore the potential maintenance of intervention effects, within-subject comparisons will be conducted with the intervention group at T3 with baseline assessment. To examine the overall intervention effects of MCAT, within-subject comparisons will be conducted by combining the baseline-to-T2 assessment scores for the intervention group and the T2-to-T3 assessment scores for the waitlist-control group. Multi-level analysis will be conducted to characterize and predict changes in all outcomes. Intervention and waitlist-control groups will also be compared on demographic characteristics and baseline measures. If necessary, these will be controlled in the analyses. Exploratory analyses on the influence of nature or work and years of professional EoL care experience on main outcomes and secondary outcomes will also be carried out. Finally, recruitment rates as well as comparisons of dropout rates and missing data in the two groups will be reported.

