**Methods:**

This is an open-label waitlist randomized controlled trial. Sixty EoL care professionals, including doctors, nurses, social workers, and personal care workers, are randomly allocated to one of two groups: (i) an intervention group that receives MCAT immediately and (ii) a waitlist-control group that receives MCAT after the intervention group completes treatment. Face-to-face self-administered outcome assessments are collected at three different time points—baseline (T1) for both groups, post-intervention (T2), and 6-week follow-up (T3) for intervention group—as well as pre-intervention (T2) and post-intervention (T3) for the waitlist-control group. The primary outcome measure is burnout, and secondary measures include emotional regulation, resilience, compassion, quality of life, and death attitudes. Between- and within-participant comparisons of outcomes are conducted, and the appropriate effect size estimates are reported. An acceptability and feasibility study is to be conducted by using a triangulation of qualitative data with framework analysis.

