### Procedures

The HCA recruitment team will be asked to distribute research information pamphlets to all eligible staff at the beginning of each recruitment round. Those who are interested to join the study will inform the HCA team and provide their verbal consent in releasing their contact information to the clinical research team. Once they recruit a sufficient number of participants for each recruitment cycle, the HCA team will forward a consolidated information sheet containing only participants’ names and telephone numbers to the clinical research team. An appointed member of the clinical research team will contact the participants and arrange a time to obtain written informed consent and conduct a face-to-face self-administrated baseline assessment (T1) followed by randomization and confirmation of the intervention schedule. Those assigned to the intervention group will attend 6-weekly MCAT sessions within 1 week after randomization; thereafter, immediate post-intervention assessment will be carried out (T2) and there will be a follow-up assessment at 6 weeks (T3). Those assigned to the waitlist-control group will complete a pre-intervention assessment at 6 weeks or after the intervention group completes all treatment procedures (T2) and thereafter attend the 6-weekly MCAT sessions followed by an immediate post-intervention assessment (T3). All MCAT interventions are conducted in the same activity room at the headquarters of HCA. Study participants' personal information will be kept confidential and only the corresponding researchers will have access to such information.

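### The planned 'overall' MCAT effect pools treated intervals only, so it adds any natural change to the treatment effect; the randomised comparison at T2 is separate and unaffected

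*Protocol article*

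**What the plan says.** The Quantitative data section of the Protocol article plans three comparisons that matter here.

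- **Randomised contrast.** The arms are compared to assess effectiveness on burnout: "Between-subject comparisons will be conducted at T2 with baseline assessment".
- **Maintenance.** The intervention arm at T3 is compared with its own baseline, described as exploring.
- **Pooled analysis.** "To examine the overall intervention effects of MCAT, within-subject comparisons will be conducted by combining the baseline-to-T2 assessment scores for the intervention group". The other part of the pool is the waitlist arm's change over its own MCAT course, from T2 to T3.

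The third analysis is not called exploratory or descriptive. The next sentence adds a multi-level analysis of changes in all outcomes, without saying that it supplies the overall effect. The abstract announces effect sizes for both kinds of comparison: "Between- and within-participant comparisons of outcomes are conducted, and the appropriate effect size estimates are reported".

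The Procedures section fixes the timing. "Those assigned to the waitlist-control group will complete a pre-intervention assessment at 6 weeks", or once the intervention arm has finished treatment; this is T2. The waitlist arm then attends MCAT and is assessed at T3.

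**The concern.** A before-after change in treated people estimates the treatment effect plus everything else that moves the score over the same six weeks: time trend, repeated completion of the same questionnaires, and some regression to the mean. A control arm exists to measure that remainder. The waitlist arm's T1-T2 interval is the only untreated interval in this trial, and the pooled analysis does not use it. No period term or subtraction is stated.

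The label is what makes this matter. An uncontrolled change reported as the overall effect of MCAT would sit beside the randomised result with equal or greater apparent authority, because it draws on treated people from both arms. The article says the results are meant to inform policy makers about effectiveness.

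**Working it through.** **The plan's own figure.** The Sample size calculation section states N = 60, 80% power, effect size 0.8, two-sided 5%, 15% attrition.

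- Normal approximation: n per arm = 2(1.960 + 0.842)² / 0.8² = 24.5, so 25. Total 50 / 0.85 = 58.8, so 59.
- Exact t-test: 26 per arm; 52 / 0.85 = 61.2, so 62.
- With 60 × 0.85 = 51 completers (25.5 per arm), power is 80.0% by t-test and 81.5% by normal approximation.

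The figure reproduces. It belongs to the between-group comparison, not to the pooled one.

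**What the pooled analysis estimates.** Let τ be the MCAT effect (the same in both arms), δ1 and δ2 the natural change in T1-T2 and T2-T3, and w the share of the pooled sample from the intervention arm.

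- Intervention arm, T1-T2: τ + δ1
- Waitlist arm, T2-T3: τ + δ2
- Pooled: τ + wδ1 + (1 − w)δ2
- Randomised contrast, T1-T2: (τ + δ1) − δ1 = τ

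If δ1 = δ2 = δ, the pooled bias is δ. If the shift occurs in the first period only, it is wδ1. With 25 of 51 from the intervention arm, w = 0.49, so about half the shift enters.

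**How often the pooled test would be significant with τ = 0.** These inputs are assumptions, not figures from the article: SD 1 at each visit, correlation ρ of 0.5 to 0.7 between visits, 51 completers, improvement of 0 to 0.4 SD per period.

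- SD of a change = √(2(1 − ρ)): 1.00 at ρ = 0.5 and 0.775 at ρ = 0.7.
- Standard error = that / √51: 0.140 and 0.108.
- Noncentrality at δ = 0.2: 0.2 / 0.140 = 1.43 and 0.2 / 0.108 = 1.84. The noncentral t distribution on 50 degrees of freedom gives 29% and 44%.

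The equal-drift column below uses this formula, and simulation (20,000 runs, 25 + 26 completers) agreed at the values checked (0, 0.2, 0.3 and 0.4 SD). The first-period column is from the same simulation.

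| Natural improvement (SD) | Pooled, same in both periods | Pooled, first period only | Randomised T1-T2 contrast |
|---|---|---|---|
| 0 | 5% | 5% | about 5% |
| 0.1 | 11-15% | not run | about 5% |
| 0.2 | 29-44% | 10-14% | about 5% |
| 0.3 | 56-77% | 17-26% | about 5% |
| 0.4 | 80-95% | 27-40% | about 5% |

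**Direction.** The bias has the sign of the drift. With τ = 0.4 and an improvement of 0.2 in each period, the pooled estimate averages 0.4 + 0.2 = 0.60. With a worsening of 0.2 it averages 0.4 − 0.2 = 0.20. The randomised contrast averages 0.40 in both cases.

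**The case against.** The strongest reply is that the trial already has a controlled test. The T2 comparison is planned, is tied to the primary outcome and is what the sample size was built on. That stands. A reader might infer that the plan discards its randomisation; the document supports this only for the one pooled analysis.

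A reader might also infer that the pooled test is bound to give the smallest p-value or the largest effect. It is not. That depends on the direction of drift, and the article's own Background describes constant exposure to death and loss leading to burnout, so worsening is possible. Nor does the article rank the pooled result as primary.

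Regression to the mean is a weak mechanism here. Staff volunteer, which makes some plausible, but no burnout threshold is required at entry and the waitlist arm's starting score is a second measurement. Four separate recruitment rounds also dilute a single calendar event. Change with time in the study and with repeat testing remains. Expectation in an open-label trial with self-report affects the randomised contrast too, so it does not separate the two analyses.

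The waitlist T2 score enters both analyses. This correlates the two estimates, so their agreement would not be independent confirmation, but it is not itself a bias.

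The multi-level analysis might be meant to handle this. Its terms may properly be left to a fuller document, so their absence is no fault. As written, however, the overall effect is assigned to the within-subject comparison.

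**Conclusion.** The point holds for the pooled analysis only. As defined, it returns the MCAT effect plus the average natural change over the treated intervals, in either direction. With no MCAT effect, the false-positive rate runs from about 11-15% (0.1 SD) to 56-77% (0.3 SD) under equal drift, and is about 10-26% for a first-period shift of 0.2-0.3 SD. These rates rest on assumed drift, correlations of 0.5 to 0.7 and 51 completers. The article gives neither drift nor correlation, and with no drift the rate is the nominal 5%. The planned between-group comparison at T2 is not affected, so the main effectiveness test is sound on this point.

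**What to change.** 1. State that conclusions on effectiveness rest on the randomised between-group contrast at T2, adjusted for T1.
2. Relabel the pooled analysis as descriptive change after MCAT (uncontrolled). Report an estimate and confidence interval, with no p-value and no effectiveness wording.
3. If a pooled effect is wanted, take it from the multi-level model already planned: all visits T1-T3, terms for period and treatment state, and the waitlist T1-T2 interval included. State its assumptions about period drift and persistence of effect, because nobody is untreated in T2-T3: the waitlist arm is in MCAT and the intervention arm is in follow-up.
4. Do not simply subtract the waitlist T1-T2 change from the pooled change. That leaves τ + (1 − w)(δ2 − δ1), which is unbiased only if drift is equal in both periods. With a first-period shift alone, a bias of about +0.49δ1 becomes about −0.51δ1.

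The cost is analysis wording only. The article reports data collection still under way (month 40 of 48), so at that stage the change could be made before analysis. The pooled figure may turn out less favourable and its interval wider.

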### Participants

The sample will comprise 60 EoL care professionals. Recruitment will be conducted at all five HCA service centers (i.e., one daycare and four satellite service centers) concurrently via four non-overlapping consecutive recruitment rounds. Each round will recruit 14 or 16 participants; seven or eight participants will be randomly assigned to one intervention group, and seven or eight participants will be randomly assigned to one control group, adhering to a waitlist RCT design. Participants will be recruited through the medical director of HCA and his appointed staff with the support of a study initiation presentation conducted by the research team during a regular monthly organization meeting with all clinical and program staff. This presentation serves as a study invitation, informing potential participants of MCAT’s basic background and essential research procedures, and includes the request for participants to keep their MCAT experiences private until study completion so as to reduce the potential for intervention contamination. Participants will be invited to join the research with the understanding that they will be given allocated time during regular working hours to participate in the MCAT intervention without any financial implications on their part; they are also assured that refusal to participate is respected and would not result in any negative consequences. Inclusion criteria include EoL care professionals (at least 21 years old) who are fluent in written and spoken English. Exclusion criteria include the inability to provide informed consent or major depression (or other mental health conditions) or both. Written informed consent will be obtained from all participants before study participation. Participants’ confidentiality will be safeguarded under this ethical provision.

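### Covariate adjustment is triggered by comparing the randomised arms at baseline, with no criterion, so the primary model is not fixed in advance; T1 is used as a repeated measure rather than the more efficient covariate

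*Protocol article*

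**What the plan says.** Three statements in the protocol article bear on this point.

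- **Adjustment rule (Quantitative data):** "Intervention and waitlist-control groups will also be compared on demographic characteristics and baseline measures. If necessary, these will be controlled in the analyses". The article does not say what makes adjustment necessary, and it names no covariate that will be used regardless.
- **Purpose of the demographic data (Demographic measures):** "To determine whether demographic variables are potential confounding factors that affect primary and secondary outcome variables". The section lists six demographic items ("age, gender, ethnicity, marital status, education, and religion") and three work items: employment type, professional role and length of EoL experience.
- **Main model (Quantitative data):** "Between- and within-subject comparisons of outcomes will be conducted by using repeated-measures analysis of variance (ANOVA"). For the comparison between arms: "Between-subject comparisons will be conducted at T2 with baseline assessment".

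Randomization is done separately within each of four recruitment rounds, with equal arms of seven or eight (Participants; Randomization). The design is open-label (Study design).

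**The concern.** Under random allocation, a difference between arms at baseline is a chance event. Testing or inspecting it cannot show whether a variable is a confounder. What makes a covariate worth having is its relation to burnout, and a rule driven by imbalance tends to pass over a strong predictor that happens to be balanced.

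A second consequence is that the primary model is open until the data have been seen. With no criterion and a long candidate list, several defensible versions of the treatment effect exist, and the reader cannot tell which one was intended.

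A related question is how the baseline burnout score is used. It is normally the best predictor of the later score (a general expectation; the article reports no correlations). Whether it enters as a covariate or as the first of two repeated measures affects precision in a trial of 60.

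**Working it through.** **1. The plan's own sample size.** Inputs from Sample size calculation: effect size 0.8 (SD 1), two-sided 5%, 80% power, 15% attrition.

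- n per arm = 2 × (1.960 + 0.842)² / 0.8² = 24.5, so 25.
- 25 / 0.85 = 29.4, so 30 per arm and **60 in total**, as stated.
- Completers: 60 × 0.85 = 51. Power at 51 is 81.5% (normal approximation) or 79.9% (t distribution).

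The sample size reproduces. It corresponds to an unadjusted comparison of two means.

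**2. How often chance would trigger adjustment.** Candidates: 6 demographic + 3 work variables = 9. Adding the 6 instruments under Outcome measures gives 15, or 17 if the MBI-GS counts as three ("The MBI-GS comprises 16 items clustered in three subscales"). *Assumptions not in the article:* the trigger is p<0.05 and the tests are independent. P(at least one) = 1 − 0.95^k.

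| k | P(at least one) | Expected number |
|---|---|---|
| 9 | 37% | 0.45 |
| 15 | 54% | 0.75 |
| 17 | 58% | 0.85 |

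A looser trigger of 0.10 would give 1 − 0.90^9 = 61% and 1 − 0.90^15 = 79%. Positive correlation between the variables would generally lower all of these.

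**3. Type I error of a mechanical rule.** Simulation with 51 completers and 6,000 runs per setting: ANCOVA if T1 differs between arms at p<0.05, otherwise a default model. Under no effect, with correlations 0.3 to 0.7, the rejection rate was 0.038 to 0.045 (change-score default) and 0.037 to 0.050 (T2-only default). There is no inflation. T1 was selected as a covariate in 4.4% to 5.3% of runs.

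**4. Change score against ANCOVA.** With two time points, the time-by-group test of a repeated-measures ANOVA is the test on change from baseline. With SD 1 and correlation ρ between T1 and T2, the residual variance is 2(1 − ρ) for change and 1 − ρ² for ANCOVA. Power = Φ(0.8 × √(25.5/2) / σ − 1.96), where 0.8 × √12.75 = 2.857. The article gives no ρ, so a range is shown.

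| ρ | σ² change | Power, change | σ² ANCOVA | Power, ANCOVA | Gap (points) |
|---|---|---|---|---|---|
| 0.3 | 1.40 | 67.5% | 0.91 | 85.0% | 17.5 |
| 0.5 | 1.00 | 81.5% | 0.75 | 91.0% | 9.5 |
| 0.7 | 0.60 | 95.8% | 0.51 | 97.9% | 2.1 |

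Using T2 alone gives 81.5% throughout.

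**5. Which feature causes the power loss.** In the simulation at effect size 0.8, power at ρ = 0.3, 0.5 and 0.7 was:

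- always change score: 66.7%, 79.9%, 95.5%;
- change score, switching to ANCOVA when T1 is imbalanced: 68.1%, 80.9%, 95.8%;
- always ANCOVA: 83.2%, 89.2%, 97.4%.

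Switching on imbalance moves power by little more than one point. Nearly all of the loss is change score against ANCOVA.

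**The case against.** The strongest reply is that the baseline score is already in the model. That is correct. A reader might infer from the conditional sentence that the best predictor is usually left out, but the article compares the arms at T2 together with baseline in a repeated-measures ANOVA, so T1 contributes in every case. What is missing is its use as a covariate.

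It follows that the power gap cannot be charged to the conditional sentence, as step 5 shows. Repeated-measures ANOVA is a standard and, under randomisation, unbiased analysis. At ρ of 0.5 or more it still meets the 80% target at the planned effect size on the normal approximation. The case for ANCOVA is one of efficiency.

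A reader might also infer that the rule inflates false positives. Applied mechanically, it does not. Selective choice among models could do so, but nothing in the article suggests that the team intends it.

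The 37% and 54% figures depend on a threshold and an independence assumption that the article does not state. Its stated purpose for the demographic data also refers to variables affecting the outcomes, so prognosis is not ignored altogether.

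Finally, a covariate list is often left to an SAP, and none is shown here. That answers a charge of omission. It does not answer this point, because the article states a rule: compare the arms, then decide. An SAP that only added a threshold would still leave adjustment dependent on chance imbalance.

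**Conclusion.** The point holds in two limited parts.

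1. **The choice of covariates depends on observed imbalance and has no criterion**, so the primary model of an open-label trial is not fixed in advance. If the trigger were p<0.05 with independent tests, chance alone would call for adjustment in about 37% (9 variables) to 54% (15 variables) of trials. The harm is an undetermined estimate, not inflated type I error.
2. **The baseline score is used less efficiently than it could be.** At effect size 0.8 with 51 completers, ANCOVA gains about 17.5, 9.5 and 2.1 percentage points of power at ρ of 0.3, 0.5 and 0.7. This rests on equal variances at T1 and T2, on the treatment effect being read from the time-by-group contrast, and on a correlation that the article does not give.

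Neither part invalidates the trial. Both should be corrected, because the article itself concedes a small sample planned around a large effect.

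**What to change.** - Delete the sentence that makes control of covariates conditional on the comparison of the arms.
- Specify the primary comparison at T2 as ANCOVA, with the T1 value of the outcome analysed as covariate and recruitment round as a factor, since randomisation is done within round. If MBI-GS subscales are analysed separately, each model takes its own T1 score.
- If the team considers another variable prognostic, for example length of EoL experience, name it before analysis and include it whatever the observed imbalance. Keep the list short for about 51 completers.
- Report baseline characteristics by arm descriptively, without tests, and reword the purpose stated under Demographic measures accordingly.

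The within-participant analyses can stay as planned.

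**Cost:** a few sentences. All variables are already collected. Four rounds use 4 − 1 = 3 degrees of freedom, and T1 uses one more, so with 51 completers the residual degrees of freedom fall from 49 to 45. The article reports data collection still under way at month 40 of 48. If the analysis has not begun, the model can still be fixed and dated beforehand. If it has, report this model as the reference analysis and state when it was chosen.
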